### Statistical analyses

Statistical analysis will be performed with IBM SPSS Statistics 19.0 (IBM, Amonk, NY). As conventional randomization is not feasible in this patient group, propensity score adjustment will be applied. Propensity scores, or the likelihood to be in the treatment condition or control condition, will be estimated with the following (pre-fracture) variables: age, gender, marital status, living situation, functional status, co morbidity, cognitive function, number of medications, need for home care, need for day care. Propensity scores will be used as an independent variable in the multivariate analysis.

Descriptive statistics will be used to describe the main characteristics of the population. For comparison between UMCG and MHG and OHW a multivariate analysis of variance (MANOVA) will be applied. The Katz index, Lawton Instrumental Activities of Daily Living (IADL) scoring list, the EQ-5D and HHS will be included as dependent variables and hospital and the propensity score as independent variables. A p-value lower than 0.05 will be considered as statistically significant.

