### Setting

The study will be executed in three hospitals in the northeastern part of the Netherlands. UMCG is a tertiary university hospital, located in the city center of Groningen. Martini Hospital Groningen (MHG) is a large teaching hospital in the southern part of the city and Ommelander Hospital Winschoten (OHW) is a smaller, rurally-located hospital situated in the town of Winschoten, 40 km east of the city of Groningen. Although these three hospitals differ in certain aspects such as size, medical specialty services and educational assignments, they all offer the same standard care for patients with a hip fracture. In the Netherlands, standard care for patients with a hip fracture is based on a national professional guideline [7]. Therefore, it can be assumed that the usual care in the three hospitals prior to the intervention study is comparable. Patients are taken to one of the hospitals on basis of proximity and availability, not based on the characteristics of the hospital. Especially with respect to the UMCG, it must be mentioned that this hospital does not only provide academic or tertiary care but due to its position as one of the few hospitals in the Northern Netherlands, also provides general (secondary) medical and surgical care. Patients admitted to UMCG for treatment will be treated in the new comprehensive care pathway. Patients transported to Martini Hospital Groningen and Ommelander Hospital Winschoten will receive care as usual.

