### Sample size

The power calculation is based on the hypothesis that 15% more patients treated with the new comprehensive care pathway compared with patients in the care-as-usual condition will have recovered at least as well at 6 months follow-up to pre-fracture levels in terms of ADL as measured with the Katz index. In order to detect this 15% difference with 80% power at a significance level of 0.05 (one-sided), 130 patients are needed in the new comprehensive care pathway condition and 130 in the usual care condition. Since a comparison will be made between UMCG and MHG as well as between UMCG and OHW, 130 patients will be included in MHG and 130 in OHW. Taking into account an expected drop out-rate of 15% a total of 450 patients have to be included.

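### A single treatment-versus-control propensity score does not guarantee balance in the two hospital-specific comparisons for which the study is sized

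*Protocol article*

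**What the plan says.** Three parts of the Protocol article bear on this.

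- **Statistical analyses, the score.** "Propensity scores, or the likelihood to be in the treatment condition or control condition, will be estimated with the following (pre-fracture) variables". Ten pre-fracture variables follow. The outcome of the score model has two categories, treatment and control.
- **Statistical analyses, the outcome model.** "For comparison between UMCG and MHG and OHW a multivariate analysis of variance (MANOVA) will be applied", with "hospital and the propensity score as independent variables". Both the MANOVA and the score are in the singular, and hospital is the factor. No pair-specific or three-category score is described.
- **Sample size, the comparisons.** "Since a comparison will be made between UMCG and MHG as well as between UMCG and OHW, 130 patients will be included in MHG", and the same number in OHW. The third group of 130 is there because two hospital-specific contrasts are wanted.

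The Setting section places UMCG in the centre of Groningen and MHG, a large teaching hospital, in the same city. OHW "is a smaller, rurally-located hospital situated in the town of Winschoten, 40 km east of the city of Groningen". On how patients reach a hospital it says: "Patients are taken to one of the hospitals on basis of proximity and availability, not based on the characteristics of the hospital". It assumes that usual care was comparable across the three hospitals before the study. It makes no such statement about the patients.

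**The concern.** A propensity score for treatment v control makes measured covariates comparable, at a given score, between UMCG patients and the mixture of MHG and OHW patients. It does not make MHG patients comparable with OHW patients at that score. If a covariate is higher at one control hospital and lower at the other, the two differences offset each other in the pooled control group. The covariate then gets little weight in the score and can stay unbalanced in both pairwise contrasts.

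Propensity adjustment is this study's only substitute for randomisation. For the comparisons that set the sample size, it could leave a measured confounder partly or almost wholly uncorrected while the report says that it was adjusted for. Differences between the control hospitals are plausible. Allocation follows proximity, one control is urban and the other rural, and the score includes variables such as marital status, living situation and need for home care, which may vary between catchments.

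**Working it through.** **1. Which contrasts is the study sized for?** Inputs from the Sample size section: 15-point difference, 80% power, one-sided 0.05, 130 per group. The control rate is not stated, so it was varied from 0.30 to 0.60.

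- Unpooled formula: n = [p1(1-p1) + p2(1-p2)] × (1.645 + 0.842)² / 0.15². At 0.55 v 0.70 this is 0.4575 × 6.185 / 0.0225 = 125.8, so 126. The pooled-variance version gives 128.
- At 0.50 v 0.65 the two versions give 132 and 134. The largest value over the range is 137 (pooled version, control rate 0.425).
- Power with 130 per group is 0.78 to 0.83. The stated 130 is reproduced within tolerance.
- Total: 3 × 130 = 390. Then 390/0.85 = 459 and 390 × 1.15 = 449, against the stated 450.

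A single two-group comparison would need 2 × 130 = 260 before dropout. The extra 130 exists only for the second hospital-specific contrast. The pairwise contrasts are therefore the ones the plan powers. The sample size itself is not at issue.

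**2. What does the single score do to those contrasts?** Monte Carlo simulation with assumed inputs:

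- 130 patients per hospital, ten covariates, no pathway effect, binary outcome with logit(Y) = ln 2 × x2.
- x2 has mean 0 at UMCG and is shifted at the control hospitals. One other, non-prognostic covariate is shifted by 0.4 SD at UMCG.
- Outcome model: linear, with hospital indicators plus the score. 1,500 to 2,000 replicates. Tests are one-sided at 0.05 in favour of the pathway.

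| x2 shift at MHG / OHW | Bias, UMCG v MHG (points) | Bias, UMCG v OHW (points) | False positives, UMCG v OHW |
|---|---|---|---|
| same shift at both (+0.3 or -0.3 SD) | at most 0.2 | at most 0.2 | 4 to 6% |
| none / 0.3 SD | about -2 (-1.8) | about +2 (+2.3) | 8 to 10% |
| +0.2 / -0.2 SD | about -3 | about +3 | 11 to 12% |
| +0.3 / -0.3 SD | -4.5 to -4.7 | +4.5 | 17% |

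- With a score estimated within each pair, the +0.3/-0.3 SD case gives bias under 0.2 points and about 4% false positives in both contrasts.
- UMCG v pooled controls with the single score is unbiased in the same case (-0.1 points).
- When only OHW is shifted, the crude UMCG v OHW bias is 4.8 points. The single score removes about half of it (4.8 - 2.3 = 2.5) but introduces about -1.8 points into UMCG v MHG.
- With shifts of +0.3/-0.3 SD, UMCG v MHG rejects in only 0.5% of replicates, because its error runs the other way.

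**3. Does the pattern depend on the outcome scale?** A second simulation used a continuous outcome, ten covariates, 130 per hospital and 600 replicates. Bias is in residual SD units, UMCG v MHG / UMCG v OHW.

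| Pattern | Crude | Single score | Pair-specific scores |
|---|---|---|---|
| Controls alike | -0.41 / -0.40 | -0.01 / -0.01 | -0.01 / -0.01 |
| Controls shifted in opposite directions | -0.40 / +0.40 | -0.37 / +0.38 | 0.00 / +0.01 |
| Only OHW shifted | 0.00 / -0.40 | +0.11 / -0.11 | +0.01 / +0.01 |
| Different covariates, equal prognostic weight | -0.30 / -0.30 | -0.01 / 0.00 | -0.01 / 0.00 |
| Different covariates, unequal prognostic weight | -0.45 / -0.08 | -0.18 / +0.18 | 0.00 / 0.00 |

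The bias ranges from nothing to nearly the whole crude difference. Pair-specific scores remove it in every pattern (at most 0.014 SD). The pooled contrast is close to unbiased throughout.

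**The case against.** **The text may mean pair-specific scores.** Within UMCG v MHG one hospital is treatment and the other control, and the same is true of UMCG v OHW. The sentence defining the score would fit a model for each pair. The article speaks of propensity scores in the plural, never says that the controls are pooled for estimation, and is a condensed account. This reading is possible. It is the less natural one, because the plan describes one MANOVA across three hospitals with one score as covariate, and in such a model a UMCG patient cannot carry two pair-specific scores.

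**A reader might infer that both pairwise comparisons will be confounded.** The documents do not support that. Bias requires MHG and OHW patients to differ from each other on measured prognostic covariates, and no case-mix by hospital is reported. When the two are alike, the single score works.

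**A reader might take 4.5 points and 17% as the expected error.** That case puts UMCG exactly midway between the controls, which is close to the worst pattern. The Setting section suggests instead two city hospitals and one rural outlier, for which the figure is about 2 points and 8 to 10%. This objection stands as to size. It does not remove the problem.

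**A reader might infer that the main hypothesis is biased.** The Abstract and Background frame it as pathway v care as usual, and that pooled contrast is unbiased under the single score. This limits the consequence to the hospital-specific contrasts, but those set the sample size. Because the two errors have opposite signs, discordant results might also alert the analyst.

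**Conclusion.** The point holds as a mismatch between the adjustment and the comparisons. On its most natural reading, the plan balances UMCG against pooled usual care and then draws two hospital-specific contrasts for which that score guarantees no balance. The pair-specific reading cannot be excluded, so confidence in the defect is moderate.

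The size cannot be known from the documents. Under the assumed shifts, bias in each pairwise contrast runs from 0 to about 4.5 points. Against the 15-point target, 2 points is 2/15 = 13% and 4.5 points is 4.5/15 = 30%. False positives for UMCG v OHW run from about the nominal 5% to 17%. The shifts, the odds ratio of 2 per SD and the restriction to one prognostic covariate that differs between the control hospitals are all assumptions. The problem should be corrected, but it does not undermine the comparison with combined usual care.

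**What to change.** State how many propensity scores are estimated and on which hospitals' patients. Then:

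- For UMCG v MHG and UMCG v OHW, estimate a separate score within each pair and analyse each pair with its own score. Alternatively, fit a three-category (multinomial) score and enter both components in the model.
- Check and report covariate balance within each pair, not only between UMCG and all controls.
- Keep the treatment-v-control score for UMCG v combined usual care only.

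The cost is two extra logistic models on variables already collected. The sample size and data collection do not change.

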### Measurements

Measurements will be taken preoperatively, perioperatively, and at 6 weeks and 3 and 6 months after surgery. Preoperative demographic data, preoperative diagnosis, height, weight, Body Mass Index and ASA classification will be recorded. Hip fractures will be classified as femoral neck fractures and pertrochanteric or intertrochanteric fractures. Average surgical time, intraoperative blood loss, in-hospital transfusion rate and complications will be recorded perioperatively. Mortality will also be recorded.

Self-reported limitations in ADL will be measured with the Katz index and Lawton Instrumental Activities of Daily Living (IADL) scoring list [8,9]. The Katz index is based on an evaluation of the functional dependence or independence of patients in bathing, dressing, going to the toilet, transferring, continence and feeding. ADL index A indicates independence in all six functions, index B independence in all but one of the six functions. Indexes C–G indicate dependence in bathing and at least one additional function. The IADL scoring list is an evaluation of the abilities of patients in eight activities: using the telephone and transportation, shopping, preparing food, housekeeping and laundry, responsibility for their own medications and handling finances. On the basis of the score patients are divided into different categories that state something about their degree of independence.

Health-related quality of life will be measured using the EQ-5D (EQ-5D™ Dutch© 1987 Euroquol Group). The EQ-5D has five dimensions: mobility, self-care, usual activities, pain/discomfort, and anxiety/depression. Each dimension is divided into three degrees of severity: no problem, some problems, and major problems. Actual quality of life must also be signed on the EQ VAS scale. The Katz index and IADL scoring list are measured at the hospital (to determine the situation before the fracture) and at 6 weeks and 6 months after the operation. The EQ-5D will be assessed on the same occasions and at 3 months after the operation.

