At the outpatient clinic, at 6 weeks and 6 months after the operation, fracture consolidation, complications and Harris Hip Score will be assessed [10]. The Harris Hip Score (HHS) is a validated functional hip score that measures four items: pain, function, range of motion and deformity, in that order of importance. A score between 90 and 100 points means an excellent outcome, a score lower than 70 means a poor outcome. Six months after the operation the living and independence situation (percentage of people living in their own home again) of the patient is evaluated.

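### The propensity score omits fracture type, and the outcome model omits the baseline values of Katz, IADL and EQ-5D, although all are collected

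*Protocol article*

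**What the plan says.** Under Statistical analyses, the protocol article names ten pre-fracture variables for the propensity score: "age, gender, marital status, living situation, functional status, co morbidity, cognitive function, number of medications, need for home care, need for day care". It states how the score is used: "Propensity scores will be used as an independent variable in the multivariate analysis". The outcome analysis is a MANOVA in which Katz, IADL, EQ-5D and Harris Hip Score "will be included as dependent variables and hospital and the propensity score as independent variables".

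Under Measurements, the article describes baseline data that go beyond this list:

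- Fracture type: "Hip fractures will be classified as femoral neck fractures and pertrochanteric or intertrochanteric fractures".
- ASA class: "Preoperative demographic data, preoperative diagnosis, height, weight, Body Mass Index and ASA classification will be recorded".
- Katz and IADL: "The Katz index and IADL scoring list are measured at the hospital (to determine the situation before the fracture"), and again at 6 weeks and 6 months.
- EQ-5D: "The EQ-5D will be assessed on the same occasions and at 3 months after the operation", which gives it an in-hospital assessment too.
- Harris Hip Score: "at 6 weeks and 6 months after the operation, fracture consolidation, complications and Harris Hip Score will be assessed", so it has no baseline value.

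**The concern.** Treatment is determined by hospital, and the three hospitals differ in size, setting and role. The Discussion defends propensity scores because they adjust for observed variables, and concedes only that unobserved ones stay uncontrolled. Fracture type is observed, is set before arrival, cannot be altered by the pathway, and both main types are enrolled. Any imbalance in it that affects recovery passes into the estimated effect although the data to prevent this are on file.

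The second gap is in the outcome model. A propensity score is built to predict hospital, not outcome. It can balance a baseline value between groups and still leave in the residual most of the outcome variance which that value explains. Where the baseline value is not in the score at all, its imbalance is not removed either.

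This is not a detail lost when the article was condensed, because both the variable list and the model terms are written out.

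**Working it through.** **1. Collected data against the adjustment set**

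| Collected at baseline | In the propensity list? | In the outcome model? |
|---|---|---|
| Fracture type | No | No |
| ASA class | Not by name; comorbidity overlaps | No |
| Pre-fracture Katz, IADL | Only if functional status means these | No |
| In-hospital EQ-5D | No quality-of-life variable listed | No |
| Harris Hip Score | No baseline exists | Not applicable |

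**2. The plan's own figure.** Sample size states 130 per group for a 15-point difference (80% power, one-sided 0.05). The control rate is not given. Assuming 30% against 45%, the usual two-proportion formula gives 128 per group, and 3 × 130 × 1.15 = 448.5, or 450 when rounded up to 150 per hospital. The present point does not change these numbers; they supply the 15-point yardstick and the group size used below.

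**3. Fracture type and the recovery difference.** Approximate bias = imbalance in share × difference in recovery between fracture types. The documents give neither, so both are assumed:

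- Low: 0.05 × 0.10 = 0.5 points
- Middle: 0.10 × 0.15 = 1.5 points
- High: 0.15 × 0.20 = 3.0 points

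That is 3% to 20% of the 15-point target (0.5/15 to 3.0/15). The direction depends on which hospital has the worse mix.

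**4. Baseline values, by simulation.** 2,000 runs; 130 per group; continuous outcome; true effect 0.3 SD; logistic propensity score entered as a covariate. Assumed: baseline imbalance 0.3 SD, age imbalance 0.2 SD, fracture-type share 55% against 45% with an effect of 0.4 SD, and a baseline coefficient ρ of 0.3, 0.5 or 0.7. Fracture type is left out of the score.

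*(a) Baseline already in the score* (Katz and IADL, if that is what functional status means):

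| ρ | Model SE, score only | Model SE, score + baseline | Reduction | Power |
|---|---|---|---|---|
| 0.3 | 0.124 | 0.123 | 0.8% | 55.6% to 56.2% |
| 0.5 | 0.116 | 0.113 | 2.6% | 61.0% to 62.6% |
| 0.7 | 0.102 | 0.094 | 7.8% | 72.2% to 77.8% |

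Bias (about -0.04 SD) and the empirical SE (0.123, 0.113, 0.094) do not change. The gain is that the reported SE comes down to the true one. The remaining -0.04 SD is fracture type (0.10 × 0.4); adding it to the score brings the bias to about 0.

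*(b) Baseline not in the score* (EQ-5D). Expected bias is -(0.3ρ + 0.04):

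| ρ | Expected bias | Simulated, score only | Simulated, score + baseline | Model SE |
|---|---|---|---|---|
| 0.3 | -0.13 | -0.131 | -0.041 | 0.127 to 0.123 |
| 0.5 | -0.19 | -0.185 | -0.038 | 0.127 to 0.112 |
| 0.7 | -0.25 | -0.249 | -0.041 | 0.127 to 0.094 |

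In (b) the baseline was simulated as unrelated, within each group, to the variables in the score. Real EQ-5D will share some information with functional status and comorbidity, so these biases lie towards the upper end for the assumed imbalance.

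**The case against.** The strongest reply is that pre-fracture function is already adjusted for. The list includes functional status among pre-fracture variables, and Katz and IADL are the only pre-fracture functional measures the article describes. This largely stands. A reader might infer that Katz and IADL are compared with no control for their own baseline; the text does not support that on its natural reading. What remains is that the measure is unnamed and that some precision is lost.

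A reader might also apply the textbook gain from baseline adjustment: a correlation of 0.5-0.7 removes 25-49% of residual variance, worth 1/(1 - r²) = 1.33 to 1.96 times the patients. That holds only for a continuous score whose baseline is not otherwise adjusted for. For Katz and IADL inside the score, the squared model-SE ratios over ρ of 0.3 to 0.7 run only from (0.124/0.123)² = 1.02 to (0.102/0.094)² = 1.18. The formula also does not carry over to the binary recovery outcome on which the sample size rests.

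It is tempting to list ASA class as an equal omission. Comorbidity partly covers it, and it is not shown to be independent of the intervention: the pathway moves the anesthesiological risk assessment to the emergency room, while usual care has a preoperative examination at an unstated time. When ASA is graded is not stated.

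One might add that recovery depends mechanically on baseline, since a survivor at Katz G cannot worsen. But that outcome already uses each patient's baseline, and excluding patients who cannot complete questionnaires makes many such patients unlikely.

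Finally, the Setting section says patients go to a hospital by proximity and availability, which gives no specific reason to expect fracture types to differ. This is fair, and it is why the bias is given as an assumed range. It does not argue against using a recorded variable.

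**Conclusion.** The point holds in a limited form. The plan fixes an adjustment set that omits fracture type, and an outcome model that omits the baseline values of Katz, IADL and EQ-5D, while collecting all of them.

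- **Fracture type** is the clearest gap: a shift of 0.5-3.0 points in the recovery difference under assumed inputs. That is small to moderate against 15 points, and avoidable.
- **EQ-5D** is the next: bias and precision are both exposed, but this is not the outcome that the sample size rests on, and the bias figures require the assumed 0.3 SD imbalance.
- **Katz and IADL**: if they are the functional-status entry, the loss is about 1-8% of the model SE. If they are not, they are in the same position as EQ-5D, so the measure needs to be named.

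The documents give no imbalance, prognostic effect or correlation, so the direction of these effects and their actual size cannot be derived from them. The omissions do not by themselves invalidate the main comparison; they leave it less well protected than the collected data allow.

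**What to change.** 1. Add fracture type (femoral neck against per- or intertrochanteric) to the propensity model.
2. State that functional status in the list is the pre-fracture Katz and IADL.
3. Enter the baseline value of Katz, IADL or EQ-5D beside the score in the model for that outcome. A joint MANOVA shares its covariates across all outcomes, so this means either one model per outcome or all three baselines entered together. The Harris Hip Score is exempt.
4. Treat ASA class as optional. If it is used, state when it is graded in each hospital.

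The cost is a few model terms from data already collected, with 130 evaluable patients per hospital planned. The sample size does not change. One caveat should be written into the plan: the article ties only Katz and IADL to the pre-fracture situation, so the in-hospital EQ-5D may reflect the acute fracture. The plan should say which state it refers to.

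### The MANOVA standard errors ignore that the propensity score is estimated, so they are too large to the extent that its ten variables predict outcome

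*Protocol article*

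**What the plan says.** Under Statistical analyses, the score for receiving the pathway rather than usual care "will be estimated with the following (pre-fracture) variables: age, gender, marital status, living situation, functional status, co morbidity, cognitive function, number of medications". The list ends with home-care and day-care need, which makes ten variables. The section continues: "Propensity scores will be used as an independent variable in the multivariate analysis". The outcome model is a MANOVA in which the Katz index, IADL list, EQ-5D and Harris Hip Score "will be included as dependent variables and hospital and the propensity score as independent variables". The software is fixed: "Statistical analysis will be performed with IBM SPSS Statistics 19.0". So is the criterion: "A p-value lower than 0.05 will be considered as statistically significant". No variance correction is mentioned.

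Under Sample size: "In order to detect this 15% difference with 80% power at a significance level of 0.05 (one-sided), 130 patients are needed" in each condition. Because UMCG is to be compared with each control hospital, "130 patients will be included in MHG and 130 in OHW".

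**The concern.** The score is fitted to the same patients who are then analysed. A standard MANOVA treats every independent variable as fixed, so its standard errors take no account of that fitting. The intuition that estimating a nuisance quantity adds uncertainty is misleading here: estimating the score reduces the sampling variation of the hospital contrast, and the model does not credit the reduction.

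If so, confidence intervals are too wide, p-values from a two-hospital comparison are too large, and the nominal 0.05 is not the level of the test performed. Precision that the data contain goes unused. The article also presents the study as adding knowledge on how to apply propensity scores, so inference from the score should be right.

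**Working it through.** **Inputs.** From Sample size: 130 evaluable patients per hospital, a 15-point difference, 80% power, one-sided 0.05. From Statistical analyses: ten score variables, four outcomes, hospital and score as independent variables. Assumed: R2, the share of outcome variance that the ten variables explain beyond the score, scanned from 0 to 0.5.

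**1. The plan's own figure.** The document gives no figure for the size of the adjusted test; its only related figure is 130 per group. The control recovery rate is not stated, so I assume one. With n = [1.645√(2p̄q̄) + 0.842√(p₁q₁ + p₂q₂)]² / 0.15² and 31% versus 46%: (1.645 × 0.688 + 0.842 × 0.680)² / 0.0225 = 1.704² / 0.0225 ≈ 129.1, rounded up to 130. The largest value over control rates of 20–70% is 136 (40% versus 55%). The figure of 130 reproduces.

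**2. Mechanism.** The logistic score equations set Σ(treatment − fitted score) × covariate to zero for each of the ten covariates. The hospital estimate, adjusted for the fitted score, is therefore nearly free of chance imbalance in them. The MANOVA residual variance still includes what they explain beyond the score.

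**3. Large-sample size.** Reported SE / true SE = 1/√(1 − R2). Two-sided size = 2[1 − Φ(1.96/√(1 − R2))]. At R2 = 0.3: √0.7 = 0.837, 1.96/0.837 = 2.34, size 1.9%.

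**4. Null simulations**, 130 versus 130, ten covariates, logistic score, linear outcome:

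| Assumed R2 | SE ratio, formula | Size, formula | SE excess, simulated | Size, simulated |
|---|---|---|---|---|
| 0 | 1.00 | 5.0% | none | about 5% |
| 0.1 | 1.05 | 3.9% | 3–5% | 4–5% |
| 0.2 | 1.12 | 2.8% | 8–13% | 2.4–3.5% |
| 0.3 | 1.20 | 1.9% | 17–23% | 1.5–3% |
| 0.4 | 1.29 | 1.1% | 24–32% | 1–2% |
| 0.5 | 1.41 | 0.6% | 28–40% | 0.6–1.4% |

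One further run at 0.4 gave a ratio of only about 1.20; the excess shrinks as the score itself carries more of the variables' prognostic value. The estimate showed no bias. Using the true score gave about 5%, which isolates the cause. Entering the ten variables directly had the same sampling SD, a matching SE and size of about 5% (3.9–6.1%).

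The four-outcome MANOVA was at least as conservative: 3.0–4.6% at 0.1, 1.2–3.0% at 0.2, 0.5–2.0% at 0.4. Dichotomised outcomes were less so: 2.6–3.7% univariately at a latent R2 of 0.4.

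**5. Power at the design effect**, one-sided 0.05, with d = 1.645 + 0.842 = 2.487 and s = √(1 − R2). Uncorrected: Φ((d − 1.645)/s). Correct SE: Φ(d/s − 1.645).

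| R2 | Uncorrected | Correct SE | Difference (points) |
|---|---|---|---|
| 0.1 | 81.3% | 83.5% | 2.2 |
| 0.2 | 82.7% | 87.2% | 4.5 |
| 0.3 | 84.3% | 90.8% | 6.5 |
| 0.4 | 86.1% | 94.1% | 8.0 |

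These figures ignore variance inflation from the correlation between score and hospital. The analysis section does not state sidedness. If its 0.05 is two-sided, the corresponding pairs are 71.1/74.6, 72.2/79.4, 73.5/84.4 and 75.2/89.4%. The shortfall from 80% then comes from the change of sidedness (70.1% at R2 = 0), not from the score.

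**6. Three hospitals, one binary score**, 3 × 130. With equal case mix in MHG and OHW, MANOVA size was 3.8% (R2 0.2) and 2.7% (0.4). With a 0.5 SD difference on a prognostic covariate it was 6.9% and 10.4%. With a weaker covariate and one outcome, a separate run gave 3.7–5.0% for differences of 0.3–0.5 SD. The SEs were still too large, by 7–19% in one set of runs and 9–22% in another. The inflation therefore comes from bias, because a treatment/control score does not balance the two control hospitals. Direct covariate entry gave 5.0–5.5% in the three-hospital settings.

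**The case against.** - **R2 is unknown.** A reader might infer that the planned test simply runs at about 1–3.5%. The document does not support that. By the formula, such a range needs R2 of about 0.14 to 0.42, and at 0.05–0.10 the size is 4.4–3.9%. This stands: the size must be stated conditionally. Appreciable R2 is plausible, since pre-fracture function is in the score and Katz and IADL are outcomes, but that is a judgement.
- **Direction.** A reader might infer that p-values are always too large. That holds for a two-hospital comparison. Hospital has three levels here, and the article describes MHG as a large city teaching hospital and OHW as a smaller rural one, so unequal case mix is conceivable. This stands: too-large SEs persist, but a conservative test is not assured.
- **Consequence.** The error makes two-hospital false positives rarer, and the one-sided 80% is met without correction. A reader might infer an underpowered plan, but the figures do not show one. What is lost is extra power.
- **Silence.** An article may leave the variance estimator to a fuller plan. This does not dispose of the point, because the procedure the article names, as ordinarily run, produces the uncorrected errors. A fuller plan could override it.
- **Remedy.** A bootstrap that refits the score rejected 5.5–6.2% at nominal 5%, so it is not plainly better. That stands, and it favours direct covariate entry.

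**Conclusion.** The point holds in conditional form. Entering the estimated score as an ordinary covariate, with "hospital and the propensity score as independent variables", gives model-based standard errors that are too large whenever the ten variables predict outcome beyond the score. Over an assumed R2 of 0.1 to 0.4, the simulated excess in a two-hospital comparison runs from about 3% to 32%, and size falls from 4–5% to 1–2%. About 2 to 8 points of power are forgone under the one-sided design assumptions. These results rest on linear outcomes, 130 evaluable patients per hospital and the assumed R2. In the three-hospital model the SEs remain too large, but the net test size can lie below or above 5%. This is a problem of correct error bars and efficiency, worth fixing because the fix is cheap. It does not show that the two-hospital estimate is biased or that the planned power is missed.

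**What to change.** Enter the ten pre-fracture variables, already needed for the score, directly beside hospital in the outcome model, with or without the score. Test size was then about 5% with two or three hospitals. It runs in the named software, needs no new data, and costs about ten model degrees of freedom.

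Alternatively, keep the score but fit it separately for UMCG versus MHG and UMCG versus OHW. Take standard errors, intervals and p-values from a bootstrap stratified by hospital that re-estimates the score in every resample, or from a stacked-equation sandwich variance. This costs some computing outside the standard menu, and the bootstrap test was slightly liberal (5.5–6.2%). Bootstrapping a single treatment/control score would not remove the three-hospital bias, which is why direct entry comes first.
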